#### Sample size of houses for entomological data collection

According to WHO guideline for malaria entomology [38], a representative sample size for entomological collections per village will be 10 houses. Thus, a total of 40 houses (10 houses per treatment arm) will be used for mosquito collection. The treatment households are dispersed over three different geographical zones (low land, mid-land, and high land). Therefore, 40 households will be randomly selected for each geographical zone. Thus, a grand total of 120 houses will be selected for sampling mosquitoes from all three zones.

#### Sample size of households for social data collection

We will use the baseline data from the 3010 households collected in the district for the socioeconomic analysis. The sample is randomly selected from a fresh list of households in the rural and semi-urban part of the district. We will follow these households and collect additional information two times (baseline, midline, and end line surveys). The data collection procedure for the social data were discussed in detail in Abro et al. (2020) (doi.org/10.1257/rct.5642-1.0).

##### Recruitment

For this study, the principal investigator (AA) will be based in the study district and form a recruitment committee. The committee will be composed of the head of local administration, representative from village HEWs, the head of local health center and the principal investigator (AA). The team will make house-to-house visits and explain the objective of the study to the candidate household heads. The list of candidate households will be separately generated from the roster containing the list of household heads of the district by the data manager (ZA). In instances where the candidate household refuses to participate, reserve candidate households will be invited to participate.

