**Methods:**

A four-armed household, cluster-randomized, controlled study will be conducted to assess the combined impact of HS, LLINs and push-pull agricultural technology (PPT) against clinical malaria in children in Ethiopia. The unit of randomization will be the household, which includes a house and its occupants. A total of 838 households will be enrolled in this study. In this trial 246 households will receive LLINs and HS, 250 will receive LLINs, HS and PPT, 175 households will receive LLINs and PPT. The remaining 167 houses which receive LLINs only will be used as control. One child aged ≤14 years will be enrolled per household in each treatment and followed for clinical malaria using active case detection to estimate malaria incidence for two malaria transmission seasons.

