**Fig. 1 Fig1:**
[figure not shown]
Flow chart of the study

In this study, a total of 167, 246, 250 and 175 houses will be included in four different treatments, treatment 1 (control, LLINs only), treatment 2 (LLINs and HS), treatment 3 (LLINs, HS and PPT) and treatment 4 (LLINs and PPT), respectively. The differences in sample size across arms is due to differences in number of households within each sub-village. To full fill the total sample size, we did the random selection based on population size of each sub-village. Census of children under 14, and above 14 years of age will be made in all 838 households selected. One child will be randomly selected from each house for annual malaria parasite survey. In addition to the annual parasite screening survey, monthly follow up will be implemented in all households to monitor clinical malaria by health extension workers. If a child moves or quits the study, we will replace the child from the same house. In instances where the whole family leaves the area, we will document them as lost to follow up.

The selected children will be checked up every month for clinical symptoms of malaria infection, splenomegaly, and development of anaemia. Blood test will be conducted if the child develops clinical symptoms. The child will also be surveyed at the beginning and end of each transmission season to estimate the prevalence of *Plasmodium species* infection, parasite density, and the prevalence of anaemia. Collections will be made from both indoor and outdoor settings.

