### Sequence generation

As described in the Section of study population all the households in the district are eligible to the treatment. The unit of randomization is the sub-village (*sub-kebele*) level. For this study, we divided the 30 villages *(Kebeles)* into 66 sub-villages/sub-kebeles. In each sub-kebele, we will obtain a fresh list of farmers, which are organized into one-to-five groups.^1^ Each *sub-kebele* will be randomly assigned into the four treatment arms.

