### Randomization

As the study area is composed of different localities (and elevations) of the district, the risk of malaria infection also varies among *kebeles* (document review from district malaria information). Therefore, the study area will be first clustered into *kebeles* and then each kebele will be clustered in to *sub-kebeles*. The randomization process will be conducted using the STATA’s *sampsi* package and using *sub-kebele* as a unit of randomization. Efforts will be made to ensure that each *kebele* receives balanced number of treatments following the standard protocol developed by Pinder et al. (2016) [14]. Stratified randomization by *sub-kebeles* will take out the kebele effect and the likelihood of chance imbalances between study arms. All entomological, epidemiological, and social studies will be conducted following the same rule described above i.e., stratified randomization. The randomization will be done by ZA to prevent selection bias by concealing the allocation sequence from the field researchers assigning sub-kebeles into the four treatment arms until the moment of assignment. Thus, both the chief investigator and the principal investigator will not be involved in the randomization process.

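### Allocation concealment is not secured at household enrolment: nothing stops refusing households from being replaced by reserves once their sub-kebele's arm is known

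*Protocol article*

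**What the plan says.** Under Sequence generation the Protocol article states: "The unit of randomization is the sub-village (*sub-kebele*) level". Thirty kebeles are divided into 66 sub-kebeles, and each sub-kebele goes to one of the four arms. The Randomization section describes the safeguard as "concealing the allocation sequence from the field researchers assigning sub-kebeles into the four treatment arms until the moment of assignment". It keeps the chief and principal investigators out of the randomisation, which the data manager carries out.

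Under Recruitment, a committee visits houses and invites them to join: "The committee will be composed of the head of local administration, representative from village HEWs, the head of local health center and the principal investigator". It does not draw the names itself: "The list of candidate households will be separately generated from the roster containing the list of household heads of the district by the data manager". The rule for those who decline is: "In instances where the candidate household refuses to participate, reserve candidate households will be invited to participate".

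The Malaria incidence data analysis section, under Statistical methods, adds a second replacement rule. A child who is lost, withdraws or declines to be in the treatment is replaced at once from a reserve list. The Blinding section accepts that house screening cannot be hidden.

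The unit of randomisation is not given consistently. The abstract says: "The unit of randomization will be the household, which includes a house and its occupants". The Study flow chart section likewise assigns treatments to households, with village as the block.

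**The concern.** Random assignment of clusters balances the clusters. It balances the households in them only if the choice of who enters is settled without knowledge of the arm. Three arms here offer free screening, push-pull seed and training, or both; the control arm offers neither. A household that knows the offer may be more or less willing to join, and the reserve that takes its place may differ from it in wealth, farming engagement or malaria risk. If this happens to different degrees in different arms, the arms differ at entry for reasons unrelated to the interventions. Analysis by assigned arm starts from the enrolled households, so it cannot recover the ones that were swapped out.

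**Working it through.** The article gives no figure to reproduce on this point. The check compares its sections and then illustrates the possible size.

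**1. How many households share an assignment.** Arm sizes (text with Fig. 1): 167 + 246 + 250 + 175 = 838, which agrees with the stated total. Sub-kebeles (Sequence generation): 66. So 838 / 66 = 12.7 households per sub-kebele on average. If the sub-kebele is the unit, learning one household's arm reveals it for about 12 others and for all reserves there.

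**2. Where concealment ends.** The Randomization section covers the assignment of sub-kebeles and stops there. Enrolment is a separate step, done by the committee under Recruitment. No section keeps that committee blind. The principal investigator takes no part in the randomisation, but is not said to be unaware of its result, and sits on the committee.

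**3. Order of steps.** No section dates household recruitment or consent. The dates given are:
- June to July 2019: census and mapping (timeline table)
- July to December 2019: epidemiological and entomological pilot (timeline table)
- From January 2020: epidemiological and entomological data collection (timeline table)
- January to February 2020: selection of study villages (timeline table)
- March 2020: randomisation (timeline table)
- May to July 2020: screening of houses (timeline table)
- September to October 2020: baseline clinical survey of the study children (Clinical evaluations)

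No enrolment or consent step is listed before March 2020. The children's clinical baseline falls after screening, so it cannot cleanly show whether the arms were comparable at entry.

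**4. Is any replacement made with the arm known?** The rule under Statistical methods replaces a child for declining the treatment. A treatment can be declined only by someone who knows what it is. That rule concerns children; the Recruitment rule concerns households and does not say whether the arm is known.

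**5. Possible size, by assumption.** Let a share q of one arm be reserves whose malaria risk is k times that of the households they replace. Let the other arm be unaffected and the true rate ratio be 1. Then the apparent rate ratio is (1 − q) + q × k.

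The Background cites a Ugandan study in which 10% more household income goes with 35.6% less malaria. If reserves are 10% richer, k = 1 − 0.356 = 0.644.
- q = 0.10: 0.90 + 0.0644 = 0.964, a spurious reduction of 3.6%
- q = 0.20: 0.80 + 0.1288 = 0.929, a spurious reduction of 7.1%

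Wider range:

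| q | k = 0.5 | k = 1.25 |
|---|---|---|
| 0.05 | 0.975 | 1.0125 |
| 0.20 | 0.90 | 1.05 |

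The bias can therefore run in either direction.

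**The case against.** The strongest reply is that the article never says recruitment follows randomisation. A census, a pilot and some data collection precede March 2020, and Sequence generation mentions a fresh list of farmers before it mentions assignment. This stands: a reader might infer that concealment is actually broken, and the text does not establish that. But listing and mapping are not consent, and nothing in the article requires consent to come first.

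A second reply is that the data manager, who is not named as a committee member, draws the candidates from a roster, and that the investigators stay out of the randomisation. These are real safeguards over who is approached first. They do not control who refuses. That the same person samples and randomises is not in itself a fault.

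Third, the abstract and the Study flow chart section make the household the unit, and then a sub-kebele's arm would not reveal every household's arm. The conflict is genuine. It does not protect enrolment, because the only concealment described covers the assignment of sub-kebeles.

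Fourth, a condensed article may leave consent timing to the full protocol. That is fair for timing alone. Here, however, the article does set out its concealment, recruitment and replacement rules, and taken together they permit entry that depends on arm.

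A reader might also take the arm sizes as evidence that enrolment depended on arm: 246 + 250 = 496 screened against 167 + 175 = 342 unscreened. The documents do not support this. Replacing each refuser with one reserve leaves the numbers unchanged. The sizes look planned: the House screening section expects about 500 houses, and the 425 farmers in the Push-pull technology section equal 250 + 175. The number of sub-kebeles per arm is not given, so chance cannot be assessed. The article's own explanation, "The differences in sample size across arms is due to differences in number of households within each sub-village", is not shown to be false.

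**Conclusion.** The point holds in a limited form: concealment is not secured at household enrolment, and the order of recruitment and randomisation is not stated. The timeline and the rule on declining treatment make recruitment after allocation likely, but this is an inference. If it is right, refusal and replacement can differ by arm in an open trial, and every comparison between arms is exposed.

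The size is unknown. The 3.6% to 7.1% illustration rests on an assumed replacement share of 10% to 20%, on replacement in one arm only, and on applying the Ugandan income figure to these households. The mechanism also takes the sub-kebele as the unit, as Sequence generation and Randomization state.

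**What to change.** In Recruitment, Sequence generation and Randomization, fix the order of steps:
1. In all 66 sub-kebeles, draw the candidate list and an ordered reserve list.
2. Obtain household consent covering any of the four arms, and draw the index child.
3. Lock the list, and only then disclose the sub-kebele arms.
4. Do not replace households or children that refuse after disclosure; amend the rule under Malaria incidence data analysis to match.
5. State one unit of randomisation, so that the abstract and the Study flow chart section agree with Sequence generation and Randomization.

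If enrolment is already complete, report candidates approached, refusals and reserves used by arm, and run a sensitivity analysis restricted to first-drawn candidates.

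The cost is low. Done in advance, it re-orders steps already planned, with no added staff or households. Done afterwards, it is one table and one sensitivity analysis. The small downside is that consent must cover all four arms, so some households may decline once their arm is disclosed, and they would not be replaced.

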### Design

#### Type of study design

A longitudinal study of four-armed household clustered randomized control trial will be conducted to estimate the incremental benefit of combining house screening, long-lasting insecticidal nets, and push-pull technology.

#### Study flow chart

The study design is summarized in a flow chart as shown in Fig. 1. The study contains four treatments randomly assigned to households with village as the blocking factor. As some houses get screening and others not, there could be a risk of diverting potentially infectious mosquitoes from screened houses to unscreened ones. Thus, to avoid such risks care will be taken to not exceed 5% of houses per village as it was recommended from previous studies from The Gambia [14]. Studies conducted in other countries confirmed that the risk of mosquito spread to unprotected houses is unlikely to increase if the proportion of houses protected is less than 10% [5, 14].

**Fig. 1 Fig1:**
[figure not shown]
Flow chart of the study

In this study, a total of 167, 246, 250 and 175 houses will be included in four different treatments, treatment 1 (control, LLINs only), treatment 2 (LLINs and HS), treatment 3 (LLINs, HS and PPT) and treatment 4 (LLINs and PPT), respectively. The differences in sample size across arms is due to differences in number of households within each sub-village. To full fill the total sample size, we did the random selection based on population size of each sub-village. Census of children under 14, and above 14 years of age will be made in all 838 households selected. One child will be randomly selected from each house for annual malaria parasite survey. In addition to the annual parasite screening survey, monthly follow up will be implemented in all households to monitor clinical malaria by health extension workers. If a child moves or quits the study, we will replace the child from the same house. In instances where the whole family leaves the area, we will document them as lost to follow up.

The selected children will be checked up every month for clinical symptoms of malaria infection, splenomegaly, and development of anaemia. Blood test will be conducted if the child develops clinical symptoms. The child will also be surveyed at the beginning and end of each transmission season to estimate the prevalence of *Plasmodium species* infection, parasite density, and the prevalence of anaemia. Collections will be made from both indoor and outdoor settings.

### Sequence generation

As described in the Section of study population all the households in the district are eligible to the treatment. The unit of randomization is the sub-village (*sub-kebele*) level. For this study, we divided the 30 villages *(Kebeles)* into 66 sub-villages/sub-kebeles. In each sub-kebele, we will obtain a fresh list of farmers, which are organized into one-to-five groups.^1^ Each *sub-kebele* will be randomly assigned into the four treatment arms.

### Randomization

As the study area is composed of different localities (and elevations) of the district, the risk of malaria infection also varies among *kebeles* (document review from district malaria information). Therefore, the study area will be first clustered into *kebeles* and then each kebele will be clustered in to *sub-kebeles*. The randomization process will be conducted using the STATA’s *sampsi* package and using *sub-kebele* as a unit of randomization. Efforts will be made to ensure that each *kebele* receives balanced number of treatments following the standard protocol developed by Pinder et al. (2016) [14]. Stratified randomization by *sub-kebeles* will take out the kebele effect and the likelihood of chance imbalances between study arms. All entomological, epidemiological, and social studies will be conducted following the same rule described above i.e., stratified randomization. The randomization will be done by ZA to prevent selection bias by concealing the allocation sequence from the field researchers assigning sub-kebeles into the four treatment arms until the moment of assignment. Thus, both the chief investigator and the principal investigator will not be involved in the randomization process.

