### Statistical methods

#### Malaria incidence data analysis

Change in clinical malaria incidence over 2 years period among the treatment and control arms will be determined using Poisson distribution. In this trial we will follow modified ITT protocol and if a child is lost from follow up, or withdraw from the study, or refuse to be included in the treatment, it will be immediately replaced by a child from the reserve list. The Relative Risk (RR) and RR Reductions (RRR) will be calculated with corresponding 95% confidence intervals to compare dichotomous variables, and difference in means will be used for additional analysis of continuous variables. Mixed effects Poisson model will be used to test the difference in incidence rates among the study arms, to determine effects of the repeated measurements within house, village, the effect of year and village-intervention interaction effects. To control the effect of clustering or village and individual level confounding factors such as gender and age, these covariates will be fitted in to random effects during analysis. If a child is diagnosed with malaria case within 28 days of the first episode with the same plasmodium species, then it will be put on treatment as part of the safety protocol, however, the case will not be included in the analysis. The prevalence of anaemia among the study participants (children) will be analysed using the guideline developed by world health organization [47]. Accordingly, all children between 6 and 59 months of age, whose Hb level is recorded between 10.0–10.9 g/dl, 8.0–9.9 g/dl and less than 8.0 g/dl will be graded as mild, moderate, and severe, respectively. In line with this we will also report community level anaemia prevalence. Thus, a prevalence of anaemia will be stated as severe if it is documented over 40% (combining mild, moderate, and severe) and moderate if the prevalence is 20–39.9%. Both malaria and anaemia prevalence data will be compared in the intervention and control houses using multilevel mixed-effects logistic regression models, taking village effects into account.

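### With 66 sub-kebeles in 30 kebeles, kebele can only be an incomplete block, so the stated removal of the kebele effect and of chance imbalance cannot hold

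*Protocol article*

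**What the plan says.** Sequence generation states "The unit of randomization is the sub-village (*sub-kebele*) level", reports that "we divided the 30 villages *(Kebeles)* into 66 sub-villages/sub-kebeles", and adds "Each *sub-kebele* will be randomly assigned into the four treatment arms". The Randomization section repeats the unit ("using *sub-kebele* as a unit of randomization"). It notes that malaria risk differs between kebeles, promises efforts towards a balanced number of treatments in each kebele, and concludes that the stratified randomisation "will take out the kebele effect and the likelihood of chance imbalances between study arms".

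The Study flow chart section names the block but gives a different unit: "The study contains four treatments randomly assigned to households with village as the blocking factor". The Abstract also makes the household the unit.

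For analysis, Malaria incidence data analysis plans a mixed effects Poisson model that covers repeated measurements within house, village, and "the effect of year and village-intervention interaction effects". The sub-kebele is not named there.

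**The concern.** A blocking factor is removed from an arm comparison by design only if every block contains every arm, in fixed proportion. Here the blocks are kebeles and the units are whole sub-kebeles, and there are too few units per block for four arms.

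This matters because the protocol itself gives between-kebele differences in malaria risk as the reason for stratifying, and the district spans 900 to 2300 m. If the sentence is taken at face value, a reader of the results may assume that the arms are balanced on kebele risk when they need not be. The analysts may also see no need to model the incomplete blocks and the randomised cluster explicitly.

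**Working it through.** **Inputs.** 30 kebeles, 66 sub-kebeles and four arms (Sequence generation). Each sub-kebele goes to one arm. The arm sizes 167 + 246 + 250 + 175 = 838 agree with the stated total (Study flow chart). The number of sub-kebeles in each kebele is not given. The plan offers no calculation behind the claim, so there is no figure to reproduce.

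**Step 1: units per block.** 66 / 30 = 2.2 sub-kebeles per kebele, against the 4 needed. One sub-kebele per arm in every kebele needs 4 × 30 = 120.

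**Step 2: complete kebeles.** Let k kebeles hold at least four sub-kebeles and the other 30 − k at least one. Then 4k + (30 − k) ≤ 66, so 3k ≤ 36 and k ≤ 12. At least 18 of 30 kebeles lack an arm. If every kebele has at least two sub-kebeles, 4k + 2(30 − k) ≤ 66 gives k ≤ 3.

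**Step 3: empty cells.** There are 30 × 4 = 120 kebele-by-arm cells. Each sub-kebele fills at most one, so at most 66 (55%) are filled and at least 54 are empty.

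**Step 4: how much kebele effect remains.** This needs assumed layouts. In a simulation (6,000 runs per setting, kebele effects normal with SD 1, arms kept near 16 to 17 sub-kebeles each), the SD of the kebele part of an unadjusted two-arm contrast was:

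| Assumed layout (all sum to 66) | No blocking | Best-effort blocking | Kebeles holding both arms of a given pair, with blocking |
|---|---|---|---|
| 24 kebeles of 2, 6 of 3 | 0.35 | 0.27 | about 7 |
| 8 of 1, 12 of 2, 6 of 3, 4 of 4 | 0.34 | 0.23 | about 9 |
| 12 of 4, 18 of 1 (most favourable) | 0.34 | 0.18 | 12 |

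Complete blocks would give 0. Blocking therefore leaves between 0.181/0.340 = 53% and 0.265/0.346 = 77% of the unblocked SD.

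**Step 5: information left within kebeles.** For v arms in blocks of k units, the efficiency factor of a balanced incomplete design is v(k − 1) / [k(v − 1)]. With v = 4 it is 4 × 1 / (2 × 3) = 0.67 for blocks of two and 4 × 2 / (3 × 3) = 0.89 for blocks of three.

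**Step 6: the interaction.** To separate a village-by-intervention effect from variation between sub-kebeles, some cells must hold two or more sub-kebeles. If no arm is repeated within a kebele, which is what balancing aims at here, every filled cell holds exactly one. The two terms then coincide. Repeating an arm within a kebele would create replication, but would leave more than 54 cells empty.

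**The case against.** Several points on the other side are fair.

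- **The household reading.** Under the wording of the Abstract and Study flow chart there are about 838 / 30 = 28 households per kebele, and four arms per kebele would fit. That is a separate contradiction. It does not rescue the quoted sentence, which stands in a section that fixes the sub-kebele as the unit.
- **No promise of complete blocks.** The plan promises only efforts at balance, and a rule for small kebeles may sit in the full protocol. This is true, but no such rule can give 66 units the property claimed.
- **Bias.** A reader might infer that the arm effects are systematically confounded with kebele risk. The documents do not support that. Assignment is random, so the problem is chance imbalance, and incomplete blocks with kebele in the model still give valid adjusted contrasts at some cost in precision.
- **Error bars that are too narrow.** A reader might infer this from the blocking claim. It does not follow: the planned model already contains village effects, and nothing uses the sentence to drop them. Intervals would be too narrow if the randomised sub-kebele were left out, which is a different omission.
- **The interaction.** Each sub-kebele has about 838 / 66 = 12.7 children with repeated visits, so cell means can be estimated. This stands. What is lacking is a way to separate the interaction from sub-kebele variation. As a random term it would act as the sub-kebele intercept.
- **Stratum wording.** The phrase on stratifying by sub-kebeles might be read as making the unit its own stratum. The surrounding text on balance within each kebele points to loose wording, so nothing is built on it.

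**Conclusion.** The claim of removal should not stand. With the sub-kebele as unit, at most 12 of 30 kebeles can be complete and at least 54 of 120 cells are empty. These bounds need only the protocol's own counts and at least one sub-kebele per kebele.

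The size of the residual (0.18 to 0.27 kebele SDs before adjustment, against about 0.35 without blocking) rests on assumed layouts. It shows that blocking helps but does not eliminate the effect. The consequence is residual random imbalance and lost precision. The planned village effects recover part of this. The remaining analytic gaps are the unnamed sub-kebele and an interaction that largely duplicates it. This is worth correcting, but it does not invalidate the trial.

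**What to change.** 1. In Randomization, withdraw the sentence. State instead that kebele is an incomplete block, and report the number of sub-kebeles per kebele and by arm.
2. Reconcile the household wording in the Abstract and Study flow chart with the sub-kebele unit.
3. In Malaria incidence data analysis, fit random intercepts for both kebele and sub-kebele, naming the latter as the randomised cluster, with altitude zone as a fixed covariate. Define the zone first: the entomological sample size section uses three zones, while Study setting and period classifies the district as mid land and low land only.
4. If a malaria-risk covariate is added, use only pre-intervention records. The baseline clinical survey (September to October 2020) follows the house screening scheduled for May to July 2020, so it is not a safe baseline. The compiled district report covers 17 kebeles, so coverage of all 30 must be checked.
5. Replace the village-by-intervention interaction with zone-by-intervention, or state that it is the sub-kebele random effect.
6. Stratify or constrain the assignment by altitude zone only if it has not been done. The timeline schedules randomisation for March 2020, so this is probably moot.

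The cost is wording changes, somewhat wider intervals and a little more analysis work. Kebele, sub-kebele and zone need no new field data; a risk covariate might.
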